# Analgesic efficacy of preemptive local wound infiltration plus laparoscopic-assisted transversus abdominis plane block versus wound infiltration in patients undergoing laparoscopic colorectal resection: study protocol for a randomized, multicenter, single-blind, noninferiority trial

**DOI:** 10.1186/s13063-019-3509-y

**Published:** 2019-07-02

**Keywords:** Colorectal surgery, Laparoscopy, Postoperative analgesia, TAP block, Wound infiltration

## Abstract

**Background:**

Transversus abdominis plane (TAP) block and wound infiltration (WI) are common locoregional anesthesia techniques for pain management in patients undergoing colorectal laparoscopic surgery. Comparative data between these two practices are conflicting, and a clear benefit of TAP block over WI is still debated. The main purpose of this study is to determine the efficacy in pain control of WI compared with WI plus laparoscopic TAP block (L-TAP) in cases of laparoscopic colorectal resection. Secondary aims are to evaluate other short-term results directly related to pain management: the need for rescue analgesic drugs, the incidence of postoperative nausea and vomiting, the resumption of gut functions, and the length of hospital stay.

**Methods/design:**

This is a prospective, randomized, controlled, two-arm, multicenter, single-blind study evaluating the efficacy of postoperative analgesic management of WI versus WI plus L-TAP in the context of laparoscopic colorectal surgery. Randomization is at the patient level, and participants are randomized 1:1 to receive either WI alone or WI plus L-TAP. Those eligible for inclusion were patients undergoing laparoscopic resection for colorectal tumor or diverticular disease at the Division of General and Hepatobiliary Surgery, Verona University, Verona, Italy, and at the Colorectal Cancer Center, Kyungpook National University, Daegu, Korea. Fifty-four patients are needed in each group to evidence a difference greater than 1 of 10 according to the numeric rating scale for pain assessment to establish that this difference would matter in practice.

**Discussion:**

The demonstration of a noninferiority of WI compared with WI plus L-TAP block would call into question TAP block usefulness in the setting of laparoscopic colorectal surgery.

**Trial registration:**

ClinicalTrials.gov, NCT03376048. Prospectively registered on 15 December 2017.

**Electronic supplementary material:**

The online version of this article (10.1186/s13063-019-3509-y) contains supplementary material, which is available to authorized users.

## Background

In colorectal surgery, one of the major innovations of the last two decades relates to the introduction of evidence-based protocols, also summarized by the concept of enhanced recovery after surgery (ERAS) programs. ERAS programs include a set of perioperative procedures designed to reduce perioperative surgical stress. Compared with traditional protocols, ERAS is associated with a significant decrease in general and surgical complications, a faster recovery of bowel function, and a shorter hospital stay [1, 2].

In an 8-year experience with an ERAS protocol in colon cancer surgery, nonopioid analgesia was suggested to be one of the strongest predictors of a shorter hospital stay [3]. A multimodal opioid-sparing analgesic approach as oral or intravenous nonopioid analgesia, wound infiltration (WI), and neural blockade techniques is associated with a reduction of postoperative nausea and vomiting (PONV); prolonged postoperative ileus (PPOI); urinary retention; somnolence; delayed mobilization; and, in the elderly, postoperative delirium [4].

Local anesthesia (LA) is widely considered an important component of multimodal analgesia. Transversus abdominis plane (TAP) block is one such intervention that consists of the injection of LA into the plane between the internal oblique and transverse abdominis muscles in the midaxillary line, halfway between the costal margin and iliac crest, where the somatic nerves from T6 to L1 run to innervate the anterior abdominal wall layers from the skin to the parietal peritoneum. As a result, TAP block reduces pain sensation deriving from the anterior abdominal wall nociceptive stimuli. The most common methods used to deliver a reliable and reproducible TAP block are the ultrasound-guided method (U-TAP), generally delivered by the anesthesiologist under ultrasound guidance, and the laparoscopically assisted method (L-TAP), performed by the surgeon with direct laparoscopic visualization of the site of injection.

A recent meta-analysis of 13 studies, including 7 randomized controlled trials (RCTs), that evaluated the efficacy of TAP block in a homogeneous population of patients undergoing laparoscopic colorectal surgery demonstrated that TAP block is associated with a significant reduction in postoperative opioid consumption in the first postoperative day (POD) together with a faster recovery of bowel function [5]. Last, TAP block performed before surgery appears to provide better analgesia than TAP block performed at the end of the surgical procedure [6].

The guidelines for perioperative care in elective colorectal surgery recently published by the Enhanced Recovery After Surgery Society strongly recommend the use of TAP block instead of thoracic epidural analgesia (TEA) even though the level of evidence, based on small RCTs, was considered moderated [7].

Our groups have been involved in studying the efficacy of TAP block for several years. In our previous prospective nonrandomized studies, we compared the efficacy of TAP block with WI alone, which demonstrated no difference in the control of pain or in the use of rescue analgesics. The main advantage of TAP block was limited to a reduced use of opioid analgesics [8, 9]. Furthermore, in a recent randomized, single-blind, noninferiority trial, we demonstrated that L-TAP block was not inferior to the ultrasound-guided technique in the context of laparoscopic colorectal surgery [10].

### Rationale for the trial

Despite the number of studies analyzing TAP block technique, no definite results have been published in the setting of laparoscopic colorectal surgery. The demonstration of a noninferiority of WI compared with WI plus TAP block would call into question its usefulness in the setting of laparoscopic colorectal surgery. This study is designed to evaluate L-TAP, the method of TAP block that is the easiest, faster, cheapest, and most reproducible. Moreover, TAP block administration in a preemptive fashion seems to make the technique more effective.

### Study aims and objectives

The key aim of this study is to determine the efficacy in pain control of local WI compared with WI plus L-TAP in cases of laparoscopic colorectal resection. The secondary purposes are to evaluate other short-term results directly related to pain management: the need for rescue analgesic drugs, the incidence of PONV, the resumption of gut functions, the occurrence of postoperative complications, and the length of hospital stay.

## Methods/design

### Trial design

This is a prospective, randomized, controlled, two-arm, multicenter, single-blind study evaluating the efficacy of postoperative analgesic management of WI versus WI plus L-TAP in the context of laparoscopic colorectal surgery. Randomization is at the patient level, and participants are randomized 1:1 to receive either WI alone or WI plus L-TAP.

The protocol aim is to demonstrate the noninferiority of WI compared with WI plus L-TAP in terms of effectiveness of pain management. We are supposing a noninferiority limit for pain assessment measured according to the numeric rating scale (NRS) of 1 of 10 as the largest difference that is clinically acceptable, so that a difference in NRS greater than 1 would matter in practice.

Patients enrolled in this trial are asked to report their pain according to NRS at rest and during cough or movements, together with the occurrence of PONV at 6 h from surgery and twice daily until POD 3. Contemporarily, the amount of rescue analgesics is recorded, with patients being educated to request additional analgesic drugs when their pain is greater than NRS 4. Resumption of gut functions, evaluated as the passage of gas and stool as well as the ability to tolerate liquid and soft diet, is also considered together with the postoperative length of hospital stay. The study flow diagram and time of collection of outcomes are shown in Figs. 1 and 2, respectively.

**Fig. 1 Fig1:**
[figure not shown]
Overview study diagram

**Fig. 2 Fig2:**
[figure not shown]
Schedule of enrollment, interventions, and assessments

This study is reported in accordance with the Standard Protocol Items: Recommendations for Interventional Trials (SPIRIT) checklist for clinical trial protocols (Additional file 1).

### Setting

Participants are recruited and operated on at the Division of General and Hepatobiliary Surgery, University of Verona Hospital Trust, Verona, Italy and at the Colorectal Cancer Center, Kyungpook National University Medical Center, Kyungpook National University, Daegu, Korea. One surgeon for each center will perform the totality of all procedures on enrolled patients. The annual caseload of laparoscopic colorectal resections for the two surgeons is approximately 200 patients.

### Study duration

The planned duration of the study is 12 months. Recruitment of patients began in April 2018 and was completed in March 2019.

### Participants

Participants are patients scheduled to undergo elective multiport laparoscopic colorectal resection for colorectal tumor or diverticular disease.

### Inclusion criteria

Aged older than 18 years and younger than 80 yearsColorectal tumor or diverticular disease as indication for surgeryAmerican Society of Anesthesiologists class I, II, or IIIBody mass index less than 35 kg/m^2^Willingness to participateProvision of written informed consent

### Exclusion criteria

Allergies or contraindication to the use of locoregional anesthesia or other analgesic drugsChronic opioid useDrug or alcohol addictionSevere psychiatric disordersCoagulopathy; uncontrolled diabetes; severe impairment of cardiovascular, lung, or renal functionNeed for abdominoperineal resectionNeed for palliative surgeryNeed for major resection other than colorectal

### Interventions

#### Induction and maintenance of anesthesia

Patients do not receive long- or short-acting sedative medication before surgery. Anesthesia is induced with short-acting agents (propofol) combined with a short-acting opioid (fentanyl or remifentanil). General anesthesia is maintained with inhalational sevoflurane or desflurane in oxygen-enriched air. Alternatively, total intravenous anesthesia with target-controlled infusion pumps and a bispectral index monitor is used. A deep neuromuscular blockade (rocuronium) is maintained with train-of-four monitoring (TOF < 3 twitch), and sugammadex is used at the end of surgery to reverse the neuromuscular blockade in order to achieve a TOF ratio > 0.9. General anesthesia entails strict glucose monitoring, maintenance of normothermia (keep body temperature > 36 °C) and a goal-directed fluid infusion. Balanced crystalloids (3–5 ml/kg/hr) is preferred to 0.9% saline and colloids, and fluid responsiveness is predicted using the stroke volume variation (with a goal of stroke volume variation < 13%).

#### Surgical technique

Colectomies for lesions located between the cecum and splenic flexure are performed using a five-port technique, and the specimen is extracted through a periumbilical incision obtained by extending the camera port or by a transverse suprapubic incision. Anterior resection, sigmoid, and left hemicolectomy are performed using a four-port technique, and the specimen is removed through a periumbilical or transverse suprapubic incision. An additional 11-mm suprapubic trocar is generally used in low anterior resection to optimize surgical field exposure. Loop ileostomy is reserved for cases in which a total mesorectal excision is performed.

#### Interventional treatment

The study is based on the concept of preemptive administration of local analgesia so that both WI and L-TAP are carried out at the beginning of the surgical procedure.

The WI group contemplates the use of a total amount of 40 ml of 0.375% ropivacaine, splitting the dose (20 ml) at the trocar and minilaparotomy sites. The infiltration is completed before each skin incision.

The total amount of anesthetic in the WI plus L-TAP group is 60 ml of 0.25% ropivacaine. First, 10 ml are used to infiltrate the trocar sites. After the positioning of the trocars and the induction of the pneumoperitoneum, bilateral TAP block under laparoscopic guidance using the “two pops technique” is carried out using 20 ml of 0.25% ropivacaine for each side. Specifically, the camera is positioned for visualization of the lateral region of the abdominal wall, and an 18-gauge laparoscopic needle is introduced under direct vision at the center of the midaxillary line between the lower costal margin and the iliac crest until the surgeon feels a “pop,” after which the surgeon injects 2 ml of normal saline to verify the correct position. At this point, after Doyle’s internal bulge sign (the bulge created when the transversus abdominis muscle with peritoneum is pushed internally) is noted, the defined amount of local anesthetic is injected. The same technique is used for the contralateral block. The remaining 10 ml are injected before skin incision at the minilaparotomy site.

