## Discussion

Perioperative multimodal analgesia uses combinations of analgesic medications that act in an additive or synergistic manner to achieve pain relief with minimal or no opiate consumption. Oral or intravenous acetaminophen and nonsteroidal anti-inflammatory drugs are widely approved as the basis of this multimodal approach because they improve postoperative pain and reduce systemic opioid consumption [11]. Even if no clear benefit has been demonstrated with tramadol administration as a substitute for opioids after colorectal surgery, some authors recommend its use as one postoperative adjunct and in a rescue analgesia treatment algorithm prior to using traditional opioids [11]. TEA is considered the gold standard in patients undergoing open colorectal surgery, but it does not seem to offer any additional clinical benefits to patients undergoing laparoscopic colorectal surgery compared with alternative analgesic technique within an ERAS program [7, 12]. Therefore, current literature no longer recommends TEA for pain control after laparoscopic colorectal surgery [7, 13, 14]. TAP block and WI have been shown to efficiently control postoperative pain, reduce postoperative opioid consumption, and facilitate bowel recovery. Comparative data between these two technics are conflicting, and a clear benefit of TAP block over WI is still debated. We previously demonstrated that adding TAP block to local WI in the setting of laparoscopic colorectal surgery and the ERAS program guaranteed a reduced use of opioid analgesics and good pain control, allowing the improvement of essential aspects of enhanced recovery pathways [8, 9]. To prove the real effectiveness of TAP block, we designed a multicenter RCT comparing WI with WI plus L-TAP. Demonstration of noninferiority of WI would call into question the role of TAP block in the setting of ERAS programs.

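### The arms share the same total ropivacaine dose but not the same wound infiltration, so the stated objective and conclusion about TAP block should be limited to a fixed-total-dose comparison

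*Protocol article*

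**What the plan says.** The Trial design section says that "participants are randomized 1:1 to receive either WI alone or WI plus L-TAP". The arm names suggest a common wound infiltration, with a block added in one arm.

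The Interventional treatment section sets out what each arm receives. The WI arm gets "a total amount of 40 ml of 0.375% ropivacaine, splitting the dose (20 ml) at the trocar and minilaparotomy sites". For the other arm, "The total amount of anesthetic in the WI plus L-TAP group is 60 ml of 0.25% ropivacaine", delivered in three parts:

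- trocar sites: "First, 10 ml are used to infiltrate the trocar sites";
- the block, which "is carried out using 20 ml of 0.25% ropivacaine for each side";
- minilaparotomy: "The remaining 10 ml are injected before skin incision at the minilaparotomy site".

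On what the result will mean, the Discussion paragraph of the Abstract says that noninferiority of WI "would call into question TAP block usefulness in the setting of laparoscopic colorectal surgery". The Rationale for the trial makes the same point. The main Discussion states the purpose more strongly: "To prove the real effectiveness of TAP block, we designed a multicenter RCT comparing WI with WI plus L-TAP". It closes by saying that noninferiority would put the role of the block in ERAS programs in doubt.

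The article nowhere says that the infiltration differs between arms, that the arms are matched on total ropivacaine, or that the conclusion applies at a fixed total dose.

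**The concern.** A reader who sees WI against WI plus L-TAP will assume that the arms differ only by the block, and that the difference in pain score measures what the block adds. By the stated volumes and concentrations, the combination arm gains the block and at the same time has a smaller and more dilute infiltration. The 6 hr comparison estimates the net result of both changes.

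What is at stake is the interpretation of a positive result. If WI is declared noninferior, the article plans to question the usefulness of TAP block in general. The same result could arise if the block added analgesia and this was offset by the smaller infiltration given with it. The trial cannot tell these explanations apart, and a clinician asking whether the block adds anything to the infiltration used in the control arm would not have an answer.

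**Working it through.** **Inputs**, all from Interventional treatment. A concentration of x% is 10x mg/ml, so 0.375% = 3.75 mg/ml and 0.25% = 2.5 mg/ml.

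**Step 1: do the stated volumes add up?**
- WI: 20 ml (trocar sites) + 20 ml (minilaparotomy) = 40 ml. This matches the stated total when the 20 ml is read as the amount per site group.
- WI plus L-TAP: 10 + 20 + 20 + 10 = 60 ml. This matches the stated total.

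**Step 2: dose by location** (mg = ml × mg/ml).

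| Location | WI | WI plus L-TAP |
|---|---|---|
| All trocar sites together | 20 × 3.75 = 75 mg | 10 × 2.5 = 25 mg |
| Minilaparotomy | 20 × 3.75 = 75 mg | 10 × 2.5 = 25 mg |
| **Wounds, total** | **40 × 3.75 = 150 mg** | **20 × 2.5 = 50 mg** |
| TAP plane | 0 mg | 2 × 20 × 2.5 = 100 mg |
| **All locations** | **150 mg** | **60 × 2.5 = 150 mg** |

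The wound infiltration differs 150:50 = 3:1 in mass, 40:20 = 2:1 in volume and 3.75:2.5 = 1.5:1 in concentration. If the 20 ml in the WI arm were read in another way, only its split between trocar sites and minilaparotomy would change. The 150 mg against 50 mg would stand.

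**Step 3: what the contrast estimates.** Let Y(w, t) be the mean NRS at 6 hr with w mg infiltrated under the corresponding regimen and t mg given by TAP. The trial estimates

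Δ = Y(150, 0) − Y(50, 100).

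Adding and subtracting Y(150, 100) gives Δ = A + B, where

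- A = Y(150, 0) − Y(150, 100), the benefit of adding L-TAP to the control-arm infiltration;
- B = Y(150, 100) − Y(50, 100), the effect of the larger infiltration when the block is present.

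Neither arm supplies Y(150, 100), so A and B cannot be estimated separately under any analysis of these two arms.

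**Step 4: consequence for noninferiority.** With the margin of 1 NRS point (Trial design; Sample size calculation), noninferiority of WI supports Δ < 1. Since A = Δ − B, it supports only A < 1 − B.

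- If infiltration dose has no effect over this range, B = 0 and the bound on A is 1, as the planned conclusion implies.
- If a larger infiltration lowers pain by b points, B = −b and the bound on A loosens to 1 + b. Noninferiority is then easier to reach than it would be against an unchanged infiltration plus L-TAP.

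The documents give no value for b and no dose-response data, so its size and even its presence are unknown.

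**The case against.** The strongest reply is that this is a coherent and fully disclosed design. Holding total ropivacaine at 150 mg prevents the combination arm from doing better merely because it receives more drug. Keeping the control-arm infiltration and adding the block would give 150 + 100 = 250 mg against 150 mg and would confound technique with total dose. The combination arm does receive wound infiltration and L-TAP, and no sentence claims that the infiltration is identical. The conclusion in the Abstract and Rationale is hedged, and the Trial design section speaks of comparing analgesic management, which is a comparison of strategies.

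Most of this stands. The fixed-total-dose question is legitimate, and if the same total placed only in the wounds is noninferior, it is reasonable to question the block's practical role at that total. What does not stand is leaving the qualification unsaid. The main Discussion's sentence on proving the block's effectiveness is broader than the contrast, and the Abstract, which carries the conclusion, gives no doses.

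A reader might infer more than the documents support:

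- *That the design is invalid or the planned conclusion wholly fails.* At a fixed total dose, the hedged conclusion remains reasonable.
- *That the trial is shown to be biased towards noninferiority.* This needs a smaller infiltration to be less analgesic over this range, which the documents do not test.
- *That this trial claims to show the effect of adding the block to WI.* The Discussion wording of that kind describes the group's earlier studies.
- *That 75 against 25 mg is given at each trocar.* These are amounts per site group, and the trocar amount is shared across the ports.

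**Conclusion.** The point holds as a mismatch between the contrast and the stated objective and conclusion. Both arms receive 150 mg of ropivacaine. At the wounds it is 150 mg in the WI arm against 50 mg in the WI plus L-TAP arm, which receives the other 100 mg by TAP. The trial therefore tests two placements of a fixed total dose, with the effect of L-TAP fully confounded with that of a smaller infiltration. Noninferiority of WI would not by itself show that L-TAP adds nothing to the control-arm infiltration.

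The dose figures rest only on the stated volumes and concentrations. The suggestion that the difference favors noninferiority is conditional on an untested assumption about infiltration dose, and no amount in NRS points can be attached to it. The validity of the randomized comparison itself is not in question here.

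**What to change.** Reconcile the objective and conclusion with the Interventional treatment section. The places are the Abstract's Discussion paragraph, Rationale for the trial, Study aims and objectives, Trial design, and the two sentences of the main Discussion on the block's effectiveness and on its role in ERAS programs.

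1. State the comparison as: noninferiority of wound infiltration alone to the same total ropivacaine dose divided between wound infiltration and L-TAP.
2. State that the arms are matched on total ropivacaine (150 mg) but not on wound infiltration (150 mg against 50 mg).
3. Limit any statement on the usefulness or role of TAP block to that fixed-total-dose comparison.

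The Discussion's description of the group's earlier studies should stay as it is, and no change to any dose is proposed.

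The cost is wording and a narrower claim. Randomization, endpoint, margin and analysis are untouched by this change, and it remains feasible although recruitment has ended.

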#### Postoperative analgesia and PONV prophylaxis

The postoperative analgesic regimen is comparable between the two groups. Intravenous acetaminophen 1000 mg is administered three times per day (every 8 hr) from the day of surgery until POD 3. Tramadol 100 mg is prescribed as the first-choice rescue analgesic, whereas ketorolac 30 mg is used when tramadol does not achieve the desired effect.

PONV prophylaxis is based on the intravenous administration of metoclopramide 10 mg every 8 hr from the day of surgery until POD 3.

